## Data Safety Monitoring Committee

Clinical Trial Unit, [name], [[contact]](mailto:[contact])

The Clinical Trial Unit of the Swiss Paraplegic Centre in Nottwil is independent of the Institute of Sports Medicine in Nottwil. They provide us with the web-based data capture software secuTrial and manage the access to data input and storage.

# ETHICAL AND REGULATORY ASPECTS

The decision of the CEC concerning the conduct of the study will be made in writing to the Sponsor-Investigator before commencement of this study. The clinical study can only begin once approval from all required authorities has been received. Any additional requirements imposed by the authorities shall be implemented.

## Study registration

The study is registered on clinicaltrials.gov with the registration number NCT 02083328. Furthermore the study is registered on kofam.ch (kofam-ID-nr. SNCTP000000874).

## Categorisation of study (revise text once English translation is provided by BAG!)

Our study is a clinical trial with the supplement caffeine. It takes part in the Category A of low risk trials as our ingested caffeine dose corresponds to the international guidelines for caffeine supplementation in exercise performance.

## Competent Ethics Committee (CEC)

The study was presented at the internal scientific study committee (EGKF) at the Swiss Paraplegic Centre in Nottwil and the scientificity and ethical considerations were approved.

No changes are made to the protocol without prior Ethic Committee and Sponsor approval, except where necessary to eliminate apparent immediate hazards to study participants.

Premature study end or interruption of the study is reported within 15 days. The regular end of the study is reported to the CEC within 90 days, the final study report shall be submitted within one year after study end. Amendments are reported according to chapter 3.10.

## Competent Authorities (CA)

Not necessary since study of category A (low risk).

## Ethical Conduct of the Study

The study will be carried out in accordance to the protocol and with principles enunciated in the current version of the Declaration of Helsinki, the guidelines of Good Clinical Practice (GCP) issued by ICH, in case of medical device: the European Directive on medical devices 93/42/EEC and the ISO Norm 14155 and ISO 14971, the Swiss Law and Swiss regulatory authority’s requirements. The CEC and regulatory authorities will receive annual safety and interim reports and be informed about study stop/end in agreement with local requirements.

Add other local requirements in case of medical device or international studies.

## Declaration of interest

The principal investigator declares that there is no conflict of interest, neither intellectual nor financial or proprietary conflict of interest.

## Patient Information and Informed Consent

The investigators will explain to each participant the nature of the study, its purpose, the procedures involved, the expected duration, the potential risks and benefits and any discomfort it may entail. Each participant will be informed that the participation in the study is voluntary and that he may withdraw from the study at any time and that withdrawal of consent will not affect his subsequent medical assistance and treatment.

The participant must be informed that his medical records may be examined by authorised individuals other than their treating physician.

All participants for the study will be provided a participant information sheet and a consent form describing the study and providing sufficient information for participant to make an informed decision about their participation in the study. The subject will get this information one week before the start of their own testing phase. So, enough time will be provided to decide whether he will participate or not.

The patient information sheet and the consent form will be submitted to the CEC and to the competent authority (as applicable) to be reviewed and approved. The formal consent of a participant, using the approved consent form, must be obtained before the participant is submitted to any study procedure.

The participant should read and consider the statement before signing and dating the informed consent form, and should be given a copy of the signed document. The consent form must also be signed and dated by the investigator (or his designee) and it will be retained as part of the study records.

## Participant privacy and confidentiality

The investigator affirms and upholds the principle of the participant's right to privacy and that they shall comply with applicable privacy laws. Especially, anonymity of the participants shall be guaranteed when presenting the data at scientific meetings or publishing them in scientific journals.

Individual subject medical information obtained as a result of this study is considered confidential and disclosure to third parties is prohibited. Subject confidentiality will be further ensured by utilising subject identification code numbers to correspond to treatment data in the computer files.

For data verification purposes, authorised representatives of the Sponsor (-Investigator), a competent authority (e.g. Swissmedic), or an ethics committee may require direct access to parts of the medical records relevant to the study, including participants’ medical history.

## Early termination of the study

The Sponsor-Investigator may terminate the study prematurely according to certain circumstances, for example:

- ethical concerns,
- insufficient participant recruitment,
- when the safety of the participants is doubtful or at risk, respectively,
- alterations in accepted clinical practice that make the continuation of a clinical trial unwise,
- early evidence of benefit or harm of the experimental intervention

## Protocol amendments

Substantial amendments are only implemented after approval of the CEC and CA respectively.

Under emergency circumstances, deviations from the protocol to protect the rights, safety and well-being of human subjects may proceed without prior approval of the sponsor and the CEC/CA. Such deviations shall be documented and reported to the sponsor and the CEC/CA as soon as possible.

All Non-substantial amendments are communicated to the CA as soon as possible if applicable and to the CEC within the Annual Safety Report (ASR).

# Background and Rationale

## Background and Rationale

Heart rate variability (HRV) analysis is a possibility to examine the functioning of the autonomic nervous system (ANS). The ANS is divided into a sympathetic and parasympathetic branch which can stimulate or inhibit the heart trough the sinoatrial node. The HRV represents the length variance of the beat to beat intervals between the individual heart rates and allows to examine the power of the two branches. During the analysis of the HRV, the low frequency represents the sympathetic whereas the high frequency represents the parasympathetic part.

The sympathetic nerves leave the spinal cord at different levels whereas the parasympathetic nerves originate from the brain stem. Therefore a lesion of the spinal cord has an effect on the sympathetic part of the ANS. The higher the lesion the more the sympathetic part is affected.

The analysis of the HRV in spinal cord injured people shows partly different results than in able-bodied subjects. In a study the low frequency component is not shown in some high level injured people [20]. Other studies discovered the sympathetic part as well in high level injured people but with a reduced power [13, 20, 32].

Because of the fact that the sympathetic nervous system doesn’t leave the spinal cord over the whole length of the spine, in low level injured people the sympathetic nervous system is only affected to the 6^th^ thoracic vertebra. A lesion under this segment hasn’t a direct effect on the cardiac innervation of the ANS. Studies examining the HRV in low level injured people show the appearance of both components but with a reduced power compared to healthy reference persons.

Hence stimulants of the ANS have an effect on the two components of HRV. The impact of caffeine, which represents such a stimulant on the HRV, have been examined already in several studies with able-bodied people [18, 25, 29, 34]. There is a wide divergence in results and the effect of caffeine on HRV in able-bodied people is not yet resolved definitively [21]. Meanwhile, the impact of caffeine on the performance shows an improvement in the short time anaerobic zone.

The effect of a caffeine supplementation on HRV in spinal cord injured people has not yet been examined whereas the performance enhancing effect in this group of people could not yet be answered conclusively.

With our study we would like to generate more knowledge on the HRV measurements in spinal cord injured people and on the effect of a caffeine supplementation on the appearance of its components in this group of people compared to able-bodied persons.

Furthermore we want to verify the performance-enhancing effect of caffeine in able-bodied people and get more knowledge on the impact in spinal cord injured people.

With the new knowledge of our study we would be a step closer to the development of a possible new classification method for sports competition in spinal cord injured people. Furthermore we will get evidence on the influence of caffeine on HRV and the effectiveness in performing trough a caffeine supplementation.

In the future HRV could be a parameter for training design or for the diagnostics of over-training in athletes. So in combination with caffeine an effective training and competition schedule could possibly be developed.

## Investigational Product (treatment, device) and Indication

Caffeine is a substance found naturally in the leaves, beans and fruits of a variety of plants and is regularly consumed by ~90% of adults. The most common dietary source of caffeine is coffee but also coca cola and energy drinks contain a high amount of caffeine.

Until 2004, caffeine was on the list of banned substances with a critical value. But then caffeine was removed from this list because of further knowledge on performance enhancing effects of caffeine at specific doses. They realized that higher doses act as performance inhibiting substances.

Caffeine is absorbed within 30 to 45 min and it exerts a variety of different effects on our body. The major effects of caffeine are an enhanced muscle contraction, elevation of epinephrine and norepinephrine and so acting as a stimulant influencing bronchodilatation, higher alertness and suppressing fatigue.

A variety of different studies showed performance enhancing effects of caffeine on exercise performance of aerobic but also on short term, high-intensity anaerobic performance. Most of the people respond with a performance enhancing effect but others act as non-responders or show some negative effects. Thus effects of caffeine intake depend on the regularity of caffeine consume as habitual consumers benefit less from caffeine intake before exercise performance. New considerations for athletes indicate to abstain from caffeine one week before the competition to get the best possible benefit from caffeine consumption.

Caffeine is classified as an A supplement which means that scientific experience showed some performance enhancing effects in a healthy trained population group. No supplement on the A-list is considered as a performance enhancing product in all situations, sports or in all different population groups.

In very high doses (>6 mg/kg body mass) caffeine can provoke some adverse effects. Side effects are known as tachycardia, tremor, sleep disturbances, headache and irregular heart rate. As our doses will be lower than these high doses such side effects won`t be expected.

## Preclinical Evidence

Not relevant.

## Clinical Evidence to Date

Since quite a while, caffeine is known as an ergogenic supplement for sports performance of able-bodied athletes. It was shown in several studies that caffeine enhances performance in short-term high-intensity exercise performance. Due to altered physical conditions after a spinal cord injury (decreased gut motility, impaired ANS, etc.) studies conducted with able-bodied subjects cannot be transferred one-to-one to wheelchair athletes. Therefore, it is compulsive to investigate the effects of caffeine on exercise performance also in wheelchair athletes. In a recent study [17] we were not able to show such performance enhancing effects in paraplegic elite athletes in a 1500m wheelchair exercise test. That`s why we want to go further to investigate the effects of caffeine on the level of the ANS.

It is known [34] that HRV is changed after the intake of caffeine in able-bodied subjects but it is also known that HRV changes after a spinal cord injury [13]. It was shown [19] that not all components of the HRV were detectable in spinal cord injured subjects. Some of these components were missing in some subjects. Therefore, it may be possible, that caffeine won`t alter the HRV because of these missing components. So, one first point is to understand, if HRV also changes after the intake of caffeine in tetraplegic and paraplegic subjects and if there are any differences between the three population groups (able-bodied subjects, tetraplegic and paraplegic subjects). It was also shown [15] that HRV is quite good reproducible in spinal cord injured subjects.

From another tetraplegic caffeine study [31] we have the information, that epinephrine and norepinephrine concentration did not increase after the intake of caffeine in tetraplegic subjects even if there was an increase in paraplegic subjects. If there is no increase of these catecholamines, it is possible that in tetraplegic patients no change in HRV and no change in exercise performance could be detected. Hence, it would be very interesting to see the correlation between the increase of the catecholamines, the change of the HRV and the effect of caffeine on exercise performance between our three different population groups.

## Dose Rationale / Medical Device: Rationale for the intended purpose in study (pre-market MD)

We have chosen to supplement our subjects with a dose of 6 mg per kg body mass. This dose corresponds to the common used dosage in studies conducted with able-bodied subjects and it also corresponds to the international guidelines given for caffeine supplementation. These guidelines recommend a dosage of 3 to 6 mg/kg body mass of caffeine. As we want to conduct our spinal cord injury study with the common used dosage from able-bodied studies we did chose a 6 mg/kg body mass dosage.

Caffeine is administrated one hour before the exercise performance test as we expect the peak concentration of methylxantines (caffeine) in our bloodstream alter this time span. Also timing of supplementation is a main interest that’s why we have chosen the same timing strategy as in able-bodied studies. If epinephrine and norepinephrine concentrations are very low at this time point, it is considered to use a longer time interval after the supplementation in future studies with spinal cord injured population groups.

The amount of caffeine will be filled in gelatine capsules.

## Explanation for choice of comparator (or placebo)

As a placebo we use mannitol filled in gelatine capsules. The same number of gelatine placebo capsules will be administrated as for the caffeine capsules. As the total amount of mannitol (a sugar) is a very low dose carbohydrate amount, no additional effect of this placebo is expected.

Mannitol is a white crystalline solid and has the same colour as caffeine filled in our gelatine capsules. It is manly used to produce tablets of medicine.

## Risks / Benefits

**Caffeine administration**: The dosage of the caffeine supplementation corresponds to the dosage recommended in international and national guidelines. Therefore, the risk of caffeine administration is a very low risk. Nevertheless some adverse effects as headache, higher heart rate, tremor, nausea or tachycardia can possibly occur.

**Placebo administration:** There is no known risk for the ingestion of mannitol as a placebo supplement.

**Blood withdrawal:** Through the repeated blood withdrawal some local inflammations can occur. These little inflammations should pass away after a few days. If there is nothing special in the subject’s anamnesis no other risks should occur.

**3-min exercise performance test:** There is always a cardiac risk during high intensive exercise. As our subjects should be healthy and physically active, this risk is minimized. Our subjects undergo a health check in advance including screening of medical history. This additional intervention should further minimize the risk factors for cardiac problems.

**HRV:** No risk for the subject because these measurements are non-invasive.

**Wearing of a breathing mask:** There is no risk for wearing a breathing mask. It shouldn`t provide any problems for breathing during the HRV measurements and during the exercise testing.

**Diabetes:** To ensure that our subjects don`t suffer from any type of diabetes without knowing it, we will previously measure blood glucose concentration (see exclusion criteria).

**Benefits:** With the maximal exercise test (VO_2max_-test) the subjects get more knowledge about their general health and about their fitness. They will get to know their maximal heart rate and also the maximal performance output as well as their respiratory parameters during the testing. After this maximal exercise test they get the possibility for a training consultation where they get tips to enhance their physical fitness or their performance. After the caffeine/placebo testing phase they will know how their body reacts on the administration of caffeine in the epinephrine and norepinephrine system but also how heart rate variability changes through caffeine supplementation. The subjects will get these informations after the end of the study. They get to know if this caffeine dose acts as an ergogenic aid in their personal performance over a 3 min time. They get some personal advice for the usage of caffeine in their own sport. Additionally they get an insight in actual research with the spinal cord injured population.

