# STUDY DESIGN

## General study design and justification of design

Our study will be conducted in a placebo-controlled, double-blind and randomised study protocol. In total every subject visits the Sport Medicine for four times whereas every visit takes 2 hours expect for the first one where only 30min are needed. Every subject has to undergo three test sessions at the Institute of Sports Medicine in Nottwil. Before these three sessions the subject will visit the Institute of Sports Medicine in Nottwil for recruitment issues which involves study informed consent and a health questionnaire with specific questions about diseases and family health history including a measurement of blood glucose level.

Then at the screening, the subjects have to perform a maximal exercise test (ramp protocol at the arm crank ergometer) to measure maximal oxygen uptake, maximal heart rate and maximal power output. After a little break, subjects have to perform a familiarization trial at the arm crank ergometer (Angio V2, Lode, Groningen, Netherlands). They have to perform exactly the same test as they have to perform later in the two test sessions.

Minimum two days and maximum two weeks later the subjects visit the Sports Medicine Nottwil for the first test session. At first, they have to answer some specific questions about sleep, recent training, recent nutritional intake and the actual health condition. Afterwards, they have to lie down for a 10 min rest where after 9 min blood pressure will be measured. HRV will be measured during 5 min the supine position and 6 min in the sitting position by means of a heart rate monitor. Paced breathing (15x/min) [12] is mandatory and will be paced through a metronome. During the HRV measurement also tidal volume will be measured. As the first HRV measurement session is finished, a venous blood withdrawal will be taken to measure catecholamine concentrations. Then, when all these measurements are completed, a supplement (either caffeine or the placebo) will be ingested in gelatine capsules. After the ingestion of these capsules, the subject has a 40 min break where they can read something or just relax. During these 40 min physical activity or the ingestion of any nutrition is prohibited.

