After these 40 min, the second HRV measurement starts. The process of this measurement is exactly the same as for the first HRV measurement. They lay down for a 10 min rest with blood pressure measurement after 9 min. Afterwards again a 5 min HRV measurement in supine position and a 6 min measurement in sitting position will be performed. Tidal volume is measured during this HRV measurement.

When this second HRV measurement session is finished, a second blood withdrawal has to be taken. That means, one hour after the ingestion of either placebo or caffeine, catecholamines are analysed for a second time. After blood sampling, the warm up can start. After the standardised warm up lactate concentration of the blood is analysed taking 10 µl of blood from the earlobe using a blood lactate analyser (Biosen, EKF diagnostic, Cardiff, Great Britain) for analysis. The subject will be asked to evaluate the warm up by rating of the perceived exertion (following the Borg scale from 6 to 20). Then the 3 min exercise test can start. During this test, respiratory parameters will be measured using a device to measure oxygen consumption (MetaMax 3B,Cortex Biophysik GmbH, Leipzig, Germany). Just after having finished these 3 min of exercising, for a second time lactate concentration will be measured and again they have to rate the exertion using the Borg scale (6 to 20).

After a short 5 min break the third HRV measurement starts. Again HRV will be measured during a 5 min time in supine position and a 6 min time in sitting position. Tidal volume will be measured during the whole HRV measurement. With this HRV measurement the first test session is finished and a second test session will be conducted at least more than two days later in a randomised order.

The first visit will take 30 min. The screening and familiarization trial will be finished in around 75 min. For the two test sessions the subject has to be at the Sports Medicine for about 90 min.

In the following chart, the two 90 min test sessions are visually displayed.

[figure not shown]

As we know from previous studies conducted with disabled subjects, the level of the lesion is one critical point. Therefore, we tried to include subjects with almost the same lesion level and sensory and motor complete lesion. This could help us to have more homogenous groups of different populations.

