## Methods of minimising bias

### Randomisation

Randomisation will be assessed by lot. 50 % of all the subjects will first conduct the placebo trial and the other 50% first the caffeine trial. With which trial they start will be assigned by lot. So, there will be an “A” lot and a “B” lot and the fortune will decide whether they have the A or the B trial first. The test administrator only knows whether they have to ingest supplement A or supplement B but he does not know which supplement it is.

Applying a significance level of 0.05 and a power of 0.8 with a difference of 7.59 and a standard deviation of 10 Watt, we receive a total sample size of 9. With inclusion of a 10% drop-out rate we obtain a total sample size of 10 subjects per group. With the three different groups (able-bodied, paraplegic and tetraplegic subjects) we have in total 30 subjects and thus 120 visits overall.

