## Procedures at each visit

**Recruitment:** The subject is visiting the Institute of Sport Medicine in Nottwil for the first time during the study period. Together with the subject the informed consent is filled in. After that the health questionnaire is answered and we check if all the inclusion and exclusion criteria are fulfilled including a blood glucose testing.

**Screening:** The subject performs a VO_2max_-Test on the arm crank ergometer for measuring the maximal rate of oxygen consumption. After that the subject has a 20-30 min break. Then the 3 min performance test of the following two testing day is carried out for familiarization purposes.

**Testing Day 1:** The subject arrives at 09:00 at the Institute of Sport Medicine in Nottwil. The check list is worked trough. After that the subject is requested to empty his bladder and in case of compression stockings to take them off. Then he puts on the heart rate belt and transfers himself in a supine position on a couch where a breathing mask is put on his mouth and his nose. The HRV and tidal volume measurements are performed. Then the breathing mask is taken off followed by taking of a blood sample at the crook of the arm and the ingestion of the capsules filled with caffeine or placebo. After that the subject has a 40 min break whereas it is not allowed to be physical active or to consume any beverage or food. According to this break, the breathing mask is put on again and the second HRV and tidal volume measurement is performed. After that a second venous blood sample is taken. Then the subject transfers himself to the arm crank ergometer where a short warming up is performed followed by taking a capillary blood sample on the ear lobe for analysing the amount of blood lactate. Then the 3 min all out performance test is performed. Afterwards the subject’s capillary blood is taken again and he has 5 min for transferring himself again on the coach and the HRV and tidal volume is measured for the last time. After this, the breathing mask and the heart rate belt are taken off.

**Testing Day 2:** The procedure of this second testing day is the same as on testing day 1 (see above) except to the kind of capsule which the subject has to ingest. So if the subject ingested the caffeine capsules on the first testing he has now to ingest the placebo capsules or the other way round.

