### Primary Analysis

For testing the first hypothesis

H_0_: m_1_ = m_2_ versus
H_1_: m_1_ ≠ m_2_
where m_1_ = performance (power output) under placebo
 m_2_ = performance (power output) under caffeine

the Wilcoxon signed-rank test will be used to compare the performance under placebo with that under caffeine for three subject groups separately.

For testing the second hypothesis

H_0_: m_1_ = m_2_ versus
H_1_: m_1_ ≠ m_2_where m_1_ = change in HRV from baseline to post-treatment under placebo treatment
 m_2_ = change in HRV from baseline to post-treatment under caffeine treatment

the Wilcoxon signed-rank test will be used to compare the performance under placebo with that under caffeine for three subject groups separately.

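### The optional training consultation is not deferred until after the two test sessions, so training may change between them and add avoidable noise to the power-output comparison

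*Protocol*

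**What the plan says.** **Consultation.** Protocol section 3.7 (Risks / Benefits) lists this among the benefits: "After this maximal exercise test they get the possibility for a training consultation where they get tips to enhance their physical fitness"; the sentence goes on to name performance as well. It then turns to what subjects learn from the caffeine and placebo phase, and of that it says: "The subjects will get these informations after the end of the study". No such hold is written for the training advice.

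**Visit content.** The Study schedule table and section 9.3 place the maximal test at visit 2. Section 9.3 follows it with a break and then: "Then the 3 min performance test of the following two testing day is carried out for familiarization purposes". No visit list contains the consultation, so its date is open.

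**Gaps.** In section 6.1, from visit 2 to session 1: "Minimum two days and maximum two weeks later the subjects visit the Sports Medicine Nottwil for the first test session". From session 1 to session 2: "a second test session will be conducted at least more than two days later in a randomised order". The first gap has a maximum; the second does not.

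**Order and analysis.** Section 6.2.1 assigns order by lot: "50 % of all the subjects will first conduct the placebo trial and the other 50% first the caffeine trial". No stratification by injury group is stated. In section 11.4.2, "the Wilcoxon signed-rank test will be used to compare the performance under placebo with that under caffeine for three subject groups separately". The opening of section 11 leaves sequence out of the analysis. It treats the period effect as negligible because a practice session precedes data collection and should remove learning.

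**Control of training.** Section 6.1 has subjects questioned about recent training at the test sessions. Section 7.4 lists the intensity of previous training among the withdrawal criteria, without a limit. Section 8.6 fixes medication dosage and standardises nutrition and caffeine intake, but does not mention training.

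**The concern.** A primary outcome is power in a 3 min all-out arm-crank test, compared within each person across two sessions. The protocol itself offers advice meant to improve performance, and as written the advice can be taken up before or between those sessions. A resulting change in training between them is a period effect.

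The stated reason for ignoring period effects covers learning of the test only. It does not cover a change in fitness or training, and the longer the second gap, the more room there is for one. At stake is some precision in groups of about 10 and, where order is uneven within a group, some bias in that group's estimate.

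**Working it through.** **Inputs.** Difference sought 7.59 and SD 10 W, alpha 0.05, power 0.8, 10% drop-out, n = 9 raised to 10 per group (section 6.2.1). Two-sided hypotheses (section 11.1). Thirty subjects in three groups of 10 (synopsis and section 6.2.1). The session 2 minus session 1 shift, d, is not in the documents; values of 2, 3 and 5 W are assumptions.

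**The plan's own figure.** The drop-out step reproduces: 9/(1 − 0.1) = 10. The 9 does not, if 10 W is the SD of paired differences: ((1.960 + 0.842) × 10/7.59)² = 13.6, so 14 (16 with the t distribution). If 10 W is instead the SD within a session, 9 needs an unstated within-person correlation of about 0.70 (normal) to 0.75 (t). This is a separate matter, but it means the SD of differences is uncertain, so both readings are carried below.

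**Step 1: which training change matters.** A gain completed before session 1 is present in both sessions and drops out of caffeine minus placebo. A change d between sessions enters as +d for a man who takes caffeine second and −d for a man who takes it first.

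**Step 2: noise with balanced order.** If every subject shifts by d, the SD of differences becomes √(SD² + d²).

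| SD of differences | d = 2 W | d = 3 W | d = 5 W |
|---|---|---|---|
| 10 W | √104 = 10.2 (+2%) | √109 = 10.4 (+4%) | √125 = 11.2 (+12%) |
| 7.75 W (correlation 0.70: 10 × √0.6) | √64 = 8.0 (+3%) | √69 = 8.3 (+7%) | √85 = 9.2 (+19%) |
| 7.07 W (correlation 0.75: 10 × √0.5) | √54 = 7.3 (+4%) | √59 = 7.7 (+9%) | √75 = 8.7 (+22%) |

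If only half take up the advice, evenly across orders, d² is halved: with SD 10 W and d = 5, √(100 + 12.5) = 10.6 W.

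**Step 3: bias with unbalanced order.** With n1 men taking caffeine second and n2 taking it first, the mean difference is biased by d × (n1 − n2)/n. At 5:5 this is 0. At 6:4 it is 0.2d, or 1.0 W at d = 5. At 7:3 it is 0.4d, or 1.2 W at d = 3 and 2.0 W at d = 5; 2.0/7.59 = 0.26 of the difference sought.

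**Step 4: how likely imbalance is.** With 15:15 over 30 subjects and no stratification, a group of 10 is split 5:5 with probability 0.30, 6:4 with 0.45, and 7:3 or worse with 0.25 (hypergeometric). If each man is drawn independently, 7:3 or worse has probability 0.34.

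**Step 5: the planned test.** Simulated two-sided Wilcoxon signed-rank test, n = 10, normal differences with SD 10 W:

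| Shift d and order | Type I error | Power at 7.59 W |
|---|---|---|
| d = 0, 5:5 | 0.047 | 0.56 |
| d = 2, 5:5 | 0.043 | 0.54 |
| d = 5, 5:5 | 0.028 | 0.46 |
| d = 5, 7:3 with most taking caffeine second | 0.058 | 0.67 |

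Under balance the unmodelled shift makes the test conservative and costs power. In the last row the higher power comes from the bias, which there runs towards caffeine.

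**The case against.** A reader might infer that the protocol gives performance advice before both sessions and so pushes power output in favour of one treatment. The documents support neither half of that. Section 3.7 describes an optional consultation without a date, and a consultation after visit 4 also fits its words. A gain made before session 1 cancels within the person. A change between sessions is neutral in expectation, because order is drawn by lot.

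A reader might also suppose that able-bodied men are new to arm cranking and would gain most. The protocol says only that they are healthy, active and not elite (section 3.8), and everyone completes a maximal test and a practice trial on the ergometer.

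Training is not uncontrolled either. It is asked about, and its intensity is a withdrawal criterion. The checklist is an appendix that is not shown, so any limits in it cannot be judged. Subjects already train at least three times a week. The values of d are hypothetical, and 5 W in every subject is a demanding assumption for optional advice.

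All of this stands and keeps the point small. It does not remove it. The body of the protocol contains no instruction to keep usual training from visit 2 to visit 4, the second gap is open-ended, and the reason given for a negligible period effect does not reach training.

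**Conclusion.** The point holds as a minor one. The protocol leaves room for a disturbance of its own making between the two sessions of a within-person comparison.

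On the 10 W reading, the SD of differences rises by 4% at d = 3 and 12% at d = 5 when every subject shifts and order is balanced. The relative rise is larger if the true SD of differences is smaller. Any bias is confined to groups with uneven order and has no predictable direction in advance. All sizes rest on an assumed d.

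The conclusion about the text needs no value of d: the statement in section 11 that the period effect is negligible is weaker than it appears, because its reason covers learning only.

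**What to change.** - **Sections 3.7 and 9.3:** state that the training consultation takes place after visit 4, and ask participants at visit 2 to keep their usual training until then. The maximal-test values themselves need not be withheld.
- **Section 6.1:** set a maximum gap between the two test sessions, for example the two weeks already used between visits 2 and 3.

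The cost is a few sentences, a somewhat longer wait for the advice and slightly tighter scheduling. No extra participants or measurements are needed, and no participant loses the benefit.
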